### Clinical data collection

At the time of randomization, baseline data will be collected from all included patients, including maternal and patient characteristics. Demographic data will include sex, birth weight, gestational age, 5-min Apgar score, surfactant therapy, prenatal corticosteroid use, premature rupture of the membrane before the onset of labor (> 18 h), singleton/multiple birth, and mode of delivery. Population characteristics will be used to compare outcomes between the two groups.

The following clinical data will be collected: continuous positive airway pressure (CPAP)-assisted time, invasive ventilator-assisted time, days of hospitalization, days on supplemental oxygen, IVH, spontaneous intestinal perforation, NEC, and ROP.

During HC treatment, respiratory support, blood sugar, blood pressure, and anthropometric data will be collected. Outcome variables and cointerventions will be recorded at 36 weeks PMA.

After discharge, one trained investigator in each center will follow up all patients at 40 weeks PMA and at 12, 26, 52, and 104 weeks corrected age. We will provide free neurodevelopmental impairment examinations to promote follow-up rates. For potential dropouts during the follow-up, we will expand the sample size by 20% and the missing data will be ignored in the analysis. The outcomes at each time point mentioned above will be collected by the investigators (Table 1).

**Table 1 Tab1:** SPIRIT figure: showing time points for enrollment, interventions, and assessment

	Study period						
	Enrollment	Allocation	Post-allocation				Close-out
Time point	At 4 weeks after birth	At 4 weeks after birth	At 36 weeks postmenstrual age	At 40 weeks postmenstrual age	At 12, 26 weeks corrected age	At 52 weeks corrected age	At 104 weeks corrected age
Enrollment:							
Eligibility screen	X						
Informed consent	X						
Demographic data	X						
Allocation		X					
Intervention:							
Hydrocortisone		X					
Placebo		X					
Assessments:							
Baseline variables assessments	X	X					
Primary outcome			X				
Secondary outcomes:							
Brain volume				X			
Others			X				
Long-term outcomes:							
Neurodevelopmental impairment, hearing loss, and blindness							X
Number of readmissions						X	
Weight, length, and head circumference				X	X	X	X
Behavioral problems, premature birth-related mortality							X

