### Participants

Inclusion criteria:
Gestational age 26^+0^ to 30^+6^ weeks and birth weight < 1500 g; andDiagnosed early BPD at day 28, based on NICHD criteria [4] and never received any glucocorticoids after birth; andOne of the following conditions:
Oxygen reduction test showing SpO_2_ < 90% with FiO_2_ > 0.3 orNoninvasive ventilation support or nasal cannula with FiO_2_ > 0.21.

Exclusion criteria included any of the following conditions:
Invasive ventilation support needed on the 28th day of life.Congenital malformations affecting pulmonary function (e.g., congenital surfactant protein deficiencies, congenital diaphragmatic hernia) or increasing the risk of death or adverse neurodevelopmental outcome (e.g., congenital cerebral malformations, congenital hydrocephalus).Chromosomal defects (e.g., trisomy 13, 18, 21).Severe infection less than 7 days before randomization (late-onset sepsis/meningitis confirmed by positive blood culture; bacterial pneumonia, confirmed by positive tracheal culture; neonatal necrotizing enterocolitis).

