### Sample size calculation

According to the data from the participating centers in the past 2 years and the data presented from the range of previous studies [27–29], the incidence of early BPD in infants with gestational age 26^+0^ to 30^+6^ weeks was 68–77%, and 40% developed moderate or severe BPD. The effect of HC therapy was assumed to reduce moderate or severe BPD (the primary endpoint) to 25% or less (number needed to treat, NNT = 5). Adopting a maximum significance level of *α* = 0.05 and a minimum test power of 80%, the number of subjects per group will be *N* = 81, which will be increased by 20% to compensate for potential dropouts during the follow-up, leading to 98 subjects per group (total 98 × 2 = 196 subjects).

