#### Secondary outcomes

Amplitude-integrated electroencephalography (aEEG). A series of aEEGs will be monitored once a week for all preterm infants after 30 weeks PMA. Sleep-wake cycles of aEEG can be classified as absent, mature, or immature according to Hellstrom-Westas [31]. The PMA of mature sleep-wake cycles occurred will be used as one of the neurodevelopmental outcomes and be compared between two groups.Intraventricular hemorrhage (IVH) > grade II and/or periventricular leucomalacia (PVL). A series of cranial ultrasound scans will be performed regularly for all preterm infants, and these results will be extracted from the medical records after enrollment. IVH > grade II and/or PVL will be used as an adverse outcome to be compared between the groups [32].Brain volume at 40 weeks PMA. Total brain volume will be detected by using the functional MRI of the brain Software Library for automatic segmentation of the T1/T2 weighted images. The mean/median total brain volumes will be compared between groups at 40 weeks.Nosocomial infection, including cultured proven sepsis, meningitis, and pneumonia. Culture-proven infection is defined as a positive culture obtained from sputum, urine, blood, or cerebrospinal fluid of infants with clinical signs of infection, and pneumonia will be confirmed by abnormal lung examination (such X-ray, CT).Neonatal necrotizing enterocolitis (NEC). Bell stage II or more and/or focal intestinal perforation diagnosed by X-ray after enrollment to hospital discharge [33].Gastrointestinal bleeding diagnosed by the contents of the digestive tract.Retinopathy of prematurity (ROP). A series of fundus examinations will be arranged after enrollment, and ROP that needs treatment in any stage will be used as an adverse outcome [34].Anthropometric indices. Body length, head circumference, and body weight at 36 weeks of PMA.Hyperglycemia. Hyperglycemia that needs to be treated with insulin (serum glucose levels ≥ 200 mg/dl) after enrollment.Hospitalization days.

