### Statistical analysis

The analyses will be based on the intention-to-treat (ITT) principle in accordance with the Consolidated Standards of Reporting Trials (CONSORT). Statistical analyses will be performed with SAS version 9.2 (SAS Institute, Cary, North Carolina). Data will be presented as the mean ± standard deviation or median and interquartile range depending on their distribution. Categorical data, including the primary outcome, will be analyzed using the chi-square test between two groups. Continuous data will be analyzed using Student’s *t* test or the Mann-Whitney test as appropriate. The effect of HC on the dichotomous outcomes will be assessed by multivariable logistic regression analysis including possible confounders, including birth weight and gestational age. Statistical results will be reported as point estimates and 95% confidence intervals.

Mid-term data analysis will be conducted after inclusion of the first 98 patients. The principal investigator will decide whether any measure should be taken in light of the results. Case report forms (CRFs) will be entered by two independent researchers to ensure accuracy.

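### Brain injury acquired before day 28 is not a dated baseline variable or a named covariate, which costs some precision and makes the long-term neurological comparison harder to interpret

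*Protocol article*

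**What the plan says.** - **Eligibility.** The Participants section excludes congenital malformations "increasing the risk of death or adverse neurodevelopmental outcome (e.g., congenital cerebral malformations, congenital hydrocephalus"). Acquired IVH or PVL is not among the exclusions.
- **Randomisation.** Stratification is by two gestational-age bands within each centre. Brain injury is not a factor.
- **Baseline data.** Clinical data collection states: "Demographic data will include sex, birth weight, gestational age, 5-min Apgar score, surfactant therapy, prenatal corticosteroid use". Membrane rupture, plurality and mode of delivery follow. The next paragraph lists IVH among the clinical data, with no time point. PVL is not listed.
- **Scans.** Under Secondary outcomes, "A series of cranial ultrasound scans will be performed regularly for all preterm infants", with results taken from the medical records after enrolment. IVH above grade II and/or PVL is itself a secondary outcome.
- **Analysis.** Dichotomous outcomes get a chi-square test and a multivariable logistic model "including possible confounders, including birth weight and gestational age". Continuous outcomes get a t test or Mann-Whitney test, with no adjustment mentioned.
- **Later outcomes.** Total brain volume is compared at 40 weeks. Cognitive and language delay (scores below 80), cerebral palsy and behaviour checklist scores are assessed at 104 weeks corrected age.

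**The concern.** The exclusion criteria accept that brain disease present before treatment predicts poor neurodevelopment, but they deal only with the congenital form. Enrolment comes four weeks after birth, by which time acquired injury may already be on the scans. The Background and Discussion make long-term neurodevelopment the main worry about postnatal steroids, so these outcomes carry the safety message.

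If the arms happen to differ in prior injury, a reader of the results will want to know by how much, and whether the two-year comparison changes once it is allowed for. With IVH undated and PVL unlisted, damage that came before the drug cannot be separated from damage that came after it. Adjusting for the undated item would risk adjusting for an outcome of treatment. The data as specified therefore supply no safe covariate, although the scans that could supply one are being done.

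**Working it through.** **Group size used.** The protocol plans 98 per arm: 81 × 1.2 = 97.2, rounded up. With 20% lost, 98 × 0.8 = 78.4, so 78 are followed. The 81 does not itself follow from 40% against 25% (two-sided 0.05, 80% power), which needs 152 per group. It fits 40% against 20%, the difference implied by the stated number needed to treat of 5 (82 per group with pooled variance, 81 by arcsine). That is a separate matter, and nothing below depends on it.

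**Assumed inputs.** The document gives no prevalence or risk figures. I assume severe IVH or PVL at entry in a fraction q = 5-15%, and delay risk d1 = 50-60% with injury and d0 = 20% without.

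1. *Chance imbalance.* The SD of the between-arm difference in prior injury is √(2q(1−q)/n).
   - q = 5%, n = 98: √(0.095/98) = 3.1 points.
   - q = 15%, n = 78: √(0.255/78) = 5.7 points.
2. *Effect on the delay comparison.* A 1-SD imbalance shifts the risk difference by SD × (d1 − d0): from 3.1 × 0.30 = 0.9 to 5.7 × 0.40 = 2.3 points.
3. *Set against sampling error.* Take q = 10%, 60% against 20%, n = 98.
   - Overall risk p = 0.1 × 0.6 + 0.9 × 0.2 = 24%.
   - Standard error = √(2 × 0.24 × 0.76/98) = 6.1 points.
   - Imbalance SD = √(0.18/98) = 4.3 points, so the shift is 4.3 × 0.40 = 1.7 points, or 0.28 of a standard error.
   - Over the whole assumed range the ratio is 0.16-0.33, so a 2-SD imbalance still moves the estimate by less than one standard error.
4. *Precision available.* R² = (d1 − d0)² q(1−q)/(p(1−p)); gain in effective sample size = 1/(1 − R²) − 1.
   - Low end (q = 5%, 50% against 20%, p = 21.5%): R² = 0.004275/0.1688 = 2.5%, gain about 3%.
   - Example in step 3: R² = 0.0144/0.1824 = 7.9%, gain 8.6%.
   - High end (q = 15%, 60% against 20%, p = 26%): R² = 0.0204/0.1924 = 10.6%, gain about 12%.
5. *Type I error.* A simulation of 400,000 trials per setting used 98 per arm, no drug effect, q = 5-20%, and risks of 50% against 20% or 60% against 15%.
   - The unadjusted test rejects in about 5.1% of trials over all randomisations.
   - Given an imbalance of at least 5 points in one direction it rejects in about 6-7%; given at least 10 points, in about 8-14%.
   - By exact binomial calculation, imbalances in either direction of at least 5 points have probability 14-42%, and of at least 10 points 0.2-9%.
   - A 1.96-SD imbalance (6-11 points) shifts the risk difference by about 2-5 points.
6. *Sensitivity.* At the extreme of that wider set (q = 20%, 60% against 15%, p = 24%), R² = 0.0324/0.1824 = 17.8%, a gain of about 22%. The gain depends heavily on the assumed figures.

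These figures are for a dichotomous delay outcome. The document gives nothing from which to size the gain for brain volume or behaviour scores.

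**The case against.** A reader might infer that chance imbalance could pass as a drug effect and so bias the safety result. The documents do not support that. Allocation is randomised, the ordinary standard error already allows for chance imbalance in unmeasured factors, and the overall false-positive rate stays near 5%. Only the conditional picture, given an observed imbalance, is affected.

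A reader might also infer that brain injury is not recorded at all. IVH is collected, serial ultrasound covers every preterm infant, and copies of medical records are kept, so status before randomisation may be recoverable.

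Other points against:

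- The quoted list is of demographic data. Table 1 has a separate row for baseline variables, and the covariate list is open. A full protocol or analysis plan, not shown, may say more. This is fair, and it limits the point. Still, the article fixes an unadjusted method for continuous outcomes, and an open list leaves the choice of covariates to be made later.
- The 3-12% is a ceiling for the inputs assumed. Prior injury overlaps with gestational age and birth weight, which are already used, and the formula is a linear-model approximation applied to logistic regression. This stands.
- The change needs regression models where simple tests are now planned, and cerebral palsy may have too few events for stable adjustment. This stands, and the fix allows for it.
- The primary outcome is untouched. This stands.

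**Conclusion.** The point holds as an inexpensive improvement. Infants with acquired severe brain injury can enter, the protocol article names no dated pre-treatment record of that injury, and the stated analyses either name other covariates or do not adjust. The loss is modest: at most about 3-12% of effective sample size for a delay outcome under the main assumptions, more only if injury is commoner or more predictive than assumed there. A 1-SD imbalance is worth 0.16-0.33 of a standard error. The larger practical benefit is interpretability: if the arms differ in prior injury, the report could show it and allow for it by a rule set in advance. There is no claim of bias or of inflated overall type I error. All prevalence and risk figures are assumptions.

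**What to change.** - **Clinical data collection:** add the worst cranial ultrasound finding up to randomisation, including PVL, taken from the existing scans, and show it by arm in the baseline table.
- **Statistical analysis, dichotomous outcomes:** prespecify a binary covariate (IVH above grade II and/or PVL before randomisation, yes or no), alongside gestational age and birth weight, in the logistic models for cognitive and language delay at 104 weeks.
- **Statistical analysis, continuous outcomes:** use linear models with the same covariates for 40-week brain volume and behaviour scores, in place of the unadjusted tests.
- **Cerebral palsy:** adjust only if the number of events allows, by a rule stated in advance, or use a penalised model.

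The cost is one case report form field and regression in place of simple tests, with possible instability where events are few. No new procedure is needed, and eligibility and treatment do not change.

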### Randomization

Eligible patients will be randomized at day 28 after birth in each center after at least one guardian provides informed consent. A list of all eligible patients not included in the study will be provided from all centers throughout the time of enrollment. This trial will be protected from selection bias by using concealed, stratified, and blocked randomization. Randomization will be stratified according to gestational age stratum (26^+0^ to 28^+6^ weeks, and 29^+0^ to 30^+6^ weeks) in each study center. Multiple birth infants will be internally randomized. The randomization procedure will be generated by using Excel software by the GCP faculty at the participating hospitals, and it will be sealed in a sequentially numbered envelope to maintain the allocation concealment. According to the allocation sequence, drug packages will be hidden and labeled sequentially. Participants will receive packaged drug in the order of recruitment. The first dose of study medication will be administered within 1 h after randomization.

The complete random sequence will be kept by the primary researcher at the affiliated hospital of Southwest Medical University. Centers will individually have emergency envelopes that contain the treatment information for patients. Emergency envelopes can be unsealed only under special conditions.

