### Outcomes

#### Primary outcome

The primary outcome is survival without moderate or severe BPD at PMA 36 weeks, which is defined as the following criteria: no respiratory support, spontaneous breathing FiO_2_ 0.21 for SpO_2_ 92%.

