#### Long-term outcomes after hospital discharge

Neurodevelopmental impairment at 104 weeks corrected age: The Bayley Scales of Infant and Toddler Development, Second Edition (BSID II) will be used in this trial.
Cognitive delay: defined as a cognitive score less than 80.Language delay: defined as a language score less than 80.Cerebral palsy and severity of cerebral palsy using the gross motor function classification system.Hearing loss requiring hearing aids at 104 weeks corrected age.Blindness at 104 weeks corrected age: vision loss with only form or shadow vision or no useful vision.Number of readmissions in the first year since the first discharge home.Weight, length, and head circumference at 40 weeks postmenstrual age and 12, 26, 52, and 104 weeks corrected age.Premature birth-related mortality from enrollment to 104 weeks corrected age.Behavioral problems (child behavior checklist) at 104 weeks corrected age. The scores on the checklist will be compared between groups.

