### Ethical and academic management

The research protocol was reviewed and approved by the Ethics Committee of Southwest Medical University, and we will not begin recruiting at other centers in the trial until local ethical approval has been obtained. The ethics committee will be responsible for supervising all procedures of the study. Prior to making any changes to the study protocol, a written application will be submitted to the ethics committee for approval, and new written informed consent will be obtained from the guardians.

An independent academic board, which is composed of competent department, data monitoring, and safety management advisors, has been implemented to oversee unwanted effects and risks, as well as the collection and management of the data. The academic board will review all research data every 3 months. Until the included patients are discharged, each potential adverse effect will be monitored and reported to the academic board within 48 h. All members of the academic board are independent of the sponsor and trial investigators and free of competing interests.

Participants, as well as the researchers, evaluators, doctors, and nurses who are responsible for screening, recruitment, dispensing medicine, and outcome assessment, will remain blinded to treatment allocations. The researchers conducting the statistical analysis will know only the group codes but not the corresponding interventions. When severe adverse effects occur, the academic board has the right to unseal emergency envelopes. The reason for unblinding and time will be recorded. We prepared an insurance policy for every participant. This will provide ancillary and posttrial care in the case of any harm resulting from participation in the clinical trial.

After consulting the academic board, the treatment will be suspended for the following conditions: (1) serious adverse reactions (death or severe infections) that occur during the testing or (2) a guardian request withdraw their infant from the study at any time and without any consequences. The primary outcome and other data collected for participants until the date of withdrawal will be used and analyzed as part of the ITT population.

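### Missing outcomes are to be ignored, which conflicts with the stated intention-to-treat principle and can bias the comparisons, chiefly at 104 weeks

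*Protocol article*

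**What the plan says.** Four statements in the protocol article bear on this.

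- **Statistical analysis:** "The analyses will be based on the intention-to-treat (ITT) principle". The primary outcome is compared by chi-square test. Dichotomous outcomes are also analysed by logistic regression with birth weight and gestational age among the covariates.
- **Clinical data collection**, in the paragraph on visits after discharge: "For potential dropouts during the follow-up, we will expand the sample size by 20% and the missing data will be ignored in the analysis". The article gives no other rule for missing outcomes.
- **Ethical and academic management**, after listing when treatment is suspended (serious adverse reactions, or a guardian's request to withdraw): "The primary outcome and other data collected for participants until the date of withdrawal will be used and analyzed as part of the ITT population".
- **Long-term outcomes after hospital discharge:** developmental, hearing, vision and behavioural outcomes at 104 weeks corrected age. The mortality item is "Premature birth-related mortality from enrollment to 104 weeks corrected age".

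On timing, "Eligible patients will be randomized at day 28 after birth in each center", and "The primary outcome is survival without moderate or severe BPD at PMA 36 weeks".

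**The concern.** ITT means that every randomized infant counts in the arm to which it was assigned. Ignoring missing values leaves out every infant whose outcome is unknown. The result is unbiased only if loss is unrelated to outcome within the arms, or to whatever the analysis adjusts for. The protocol offers no such argument; its remedy is a larger sample, which deals with precision only.

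Two groups are affected. At 104 weeks, developmental scores will exist only for survivors who attend. Neurodevelopmental harm is the main safety question for a postnatal steroid, so selective attendance there matters. At 36 weeks PMA, an infant withdrawn earlier stays in the ITT population under one section, has no primary outcome, and is ignored under another. The article does not say how that infant counts.

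The mortality item adds to the difficulty. Developmental scores among survivors must be read beside deaths, but a count limited to deaths judged birth-related requires attribution of cause and may leave some deaths out.

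**Working it through.** **1. The plan's own allowance.** Sample size calculation: 81 evaluable per group, increased by 20%. 81 × 1.2 = 97.2, rounded up to 98, as stated. If exactly 20% are lost, 98 × 0.8 = 78.4 remain, slightly under 81; the loss that leaves 81 is 1 − 81/98 = 17.3%. So the allowance roughly preserves the number analysed. Nothing in it concerns who is lost.

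**2. Time at risk before the primary outcome.** Gestational age is 26+0 to 30+6 weeks. Adding 28 days gives PMA 30+0 to 34+6 at randomization. From there to 36+0 is 6 weeks at the longest and 8 days at the shortest. The 104-week outcomes come about two years later.

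**3. What the data cannot exclude.** Let a fraction m be missing in each arm and d be the observed difference in failure (control minus HC). The extreme bounds are (1 − m)d − m and (1 − m)d + m, so their width is 2m whatever the observed rates.

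- m = 20%: width 40 points. With the protocol's planning rates of 40% and 25% (d = 15 points), the bounds are 0.8 × 15 − 20 = −8 and 0.8 × 15 + 20 = +32.
- m = 5%: width 10 points. The bounds are 0.95 × 15 − 5 = +9.25 and 0.95 × 15 + 5 = +19.25.

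The document gives no 104-week event rates, so only the 40-point width carries over to that time point. The 5% case is an assumed lower loss, to show how the position eases at 36 weeks.

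**4. Size of bias under stated assumptions.** The loss rates and the outcomes of lost infants are assumed. The 25% and 40% are the planning rates, taken as failure rates among infants observed.

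| Scenario | True rates | True difference | Reported difference | Bias |
|---|---|---|---|---|
| 10% of HC lost, 70% of them fail; no loss in control | HC 0.9 × 25 + 0.1 × 70 = 29.5%; control 40% | 10.5 | 15 | 4.5 points |
| Same loss in both arms | HC 29.5%; control 0.9 × 40 + 0.1 × 70 = 43% | 13.5 | 15 | 1.5 points |

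With loss in HC only, the bias is (fraction lost) × (failure rate of the lost − 25%). It runs from 0.05 × (50 − 25) = 1.25 points to 0.15 × (90 − 25) = 9.75 points across 5–15% lost and 50–90% of them failing.

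**5. Direction.** Take true failure of 40% and 25% (difference 15 points), with 20% lost per arm.

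- Loss unrelated to outcome: the reported difference is 15.0 points.
- HC failures lost at 40% and HC successes at 13.33%, with control loss unrelated to outcome: HC failure appears as 0.15/0.80 = 18.75%, and the difference as 21.3 points.
- Control failures lost at 35% and control successes at 10%, with HC loss unrelated to outcome: control failure appears as 0.26/0.80 = 32.5%, and the difference as 7.5 points.

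The error can favour either arm.

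**The case against.** The strongest reply is that the rule stands in the post-discharge paragraph, is about dropouts during follow-up, and hardly touches a primary outcome assessed within weeks. Much of this stands, and applying 20% loss to the 36-week outcome would be too harsh. But the same 20% was added to the sample size for the primary endpoint, and no other rule covers an unknown 36-week status.

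The adjusted logistic regression also helps, so far as loss depends on birth weight or gestational age. It does not cover loss that follows the infant's later course, and the chi-square test has no such protection.

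A reader might go further and infer any of the following. The document does not support them.

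- *That using data up to withdrawal itself contradicts ITT.* It does not. Those infants are kept in the ITT population, and later data may be unobtainable if a guardian refuses. The difficulty arises only in combination with ignoring missing values.
- *That infants whose drug is stopped for severe infection leave follow-up and are dropped.* The text says that treatment is suspended, and its data rule speaks of withdrawal. Elsewhere all patients are to be followed. The wording is ambiguous because one paragraph covers both situations, but it does not state that these infants are lost.
- *That deaths before 36 weeks are ignored.* The primary outcome is survival without moderate or severe BPD, so such deaths already count as failures.
- *That HC will look better than it is.* That needs loss of poor outcomes to be greater in the HC arm, which is an assumption.

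Finally, details of an imputation model commonly belong in an analysis plan, and their absence here is no fault. The point is that the article states a rule, and that rule conflicts with ITT.

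**Conclusion.** The point holds in a limited form. A stated complete-case rule conflicts with the stated ITT principle, and the 20% enlargement does not answer the conflict. The comparisons can be biased; whether they will be, by how much and in which direction cannot be determined from the document.

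Exposure is chiefly at 104 weeks. If the planned 20% dropout occurred in each arm, extreme-case bounds on a risk difference would be 40 points wide. At 36 weeks PMA it is smaller and comes from infants withdrawn before assessment; with an assumed 5% missing and the planning rates, the bounds keep their sign. The 4.5-point illustration is 30% of the 15-point planning difference (4.5/15), but it depends on loss in the HC arm alone; equal loss in both arms leaves about 1.5 points.

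**What to change.** 1. **Clinical data collection and Statistical analysis.** Replace the instruction to ignore missing data with an analysis of all randomized infants. Use multiple imputation for unknown 36-week and 104-week outcomes, by arm, with gestational age, birth weight and last recorded respiratory status. Confirm that death before 36 weeks is a failure; do not impute developmental scores for infants known to have died. Add a tipping-point or best/worst-case analysis, since imputation itself assumes that the recorded variables explain the loss.
2. **Ethical and academic management.** Separate stopping study drug from withdrawal of consent for data collection. Infants who only stop the drug should still contribute 36-week and 104-week outcomes.
3. **Long-term outcomes after hospital discharge.** Report all-cause mortality to 104 weeks, alongside or instead of birth-related mortality, so that survivor-only scores can be read with deaths. A death-or-impairment composite is an optional supportive analysis.

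The cost is wording and some analysis work. Item 2 is best settled before follow-up ends, because outcomes not collected then cannot be recovered.
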